### 2.9. Monitoring and auditing

The principal investigator will designate monitoring personnel to monitor the study to ensure that the study is being conducted safely and in accordance with both the protocol and the Clinical Research Act, and that data are being collected accurately. The person in charge of monitoring will report the monitoring results to the principal investigator. No audit is applicable to this study.

### 2.10. Harms

Adverse event is defined as illness, disability, death, or infection suspected to be attributed to conducting the study, including unintended physical signs, clinically significant changes in laboratory data, and worsening of symptoms or complications. In the event of harms, the principal investigator or sub-investigator will take appropriate actions to ensure the safety of study participants, including giving treatments and discontinuing administration of the research drugs to study participants.

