## 2. Methods/design

### 2.1. Study design

This is a multicenter, exploratory, crossover, single-blind, placebo-controlled, and randomized comparative study.

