### 2.6. Interventions

Icatibant (30 mg) and placebo (saline, 3 mL) will be subcutaneously injected in a defined order in a crossover manner. Dermal pain induced by thermal load will be assessed before and after administration of both drugs. For blinding, study participants wear an eye mask when receiving the drugs. The investigator will ensure that the study participant has properly donned the eye mask before preparing the drugs and giving them to the participants. After the used syringes are discarded, the participant will be allowed to remove the eye mask. The study will be conducted over 3 consecutive days under hospitalization.

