#### 2.7.3. Adverse events.

Safety concerns in this study are assumed to be associated with the administration of icatibant and the induction of dermal pain by thermal stimuli. Safety will be assessed by monitoring adverse events, physical findings, and changes in vital signs. If an adverse event is clinically suspected, physicians will conduct a thorough examination and safety evaluation.

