#### 2.8.5. Safety assessments.

In the population of study subjects who receive at least 1 study treatment, the number and incidence of adverse events and the number of subjects suffering from adverse events will be investigated in each phase of the icatibant and placebo treatment.

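### Section 2.10 counts an occurrence as an adverse event only if the study is suspected as its cause, so the by-phase safety table in 2.8.5 rests on an attribution judgement with no described blinding

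*Protocol article*

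**What the plan says.** Section 2.10 (Harms) gives the only definition of an adverse event in the article: "Adverse event is defined as illness, disability, death, or infection suspected to be attributed to conducting the study". It continues with "including unintended physical signs, clinically significant changes in laboratory data, and worsening of symptoms or complications".

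Section 2.8.5 uses the same term for the safety analysis: among subjects who received at least one study treatment, "the number and incidence of adverse events and the number of subjects suffering from adverse events will be investigated in each phase" of icatibant and placebo treatment. No test, margin or decision rule is attached.

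On assessment, section 2.7.3 says: "If an adverse event is clinically suspected, physicians will conduct a thorough examination and safety evaluation". It names two foreseen sources of harm, the drug and the heat-induced pain, and also provides for monitoring of physical findings and vital signs.

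On masking, section 2.1 calls the trial single-blind, and section 2.6 says: "For blinding, study participants wear an eye mask when receiving the drugs". The investigator handles the drug: "The investigator will ensure that the study participant has properly donned the eye mask before preparing the drugs and giving them to the participants".

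**The concern.** A placebo phase shows the background rate of untoward events only if they are recorded without first asking what caused them. Here the causal question comes first: an occurrence not suspected to be due to the study is not an adverse event and enters neither phase's count.

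Two things follow. The incidence in both phases may be understated. In addition, the threshold for suspicion may differ between phases, because nothing in the article keeps the person judging attribution from knowing which injection was given. If it does differ, equal true incidence could appear as unequal reported incidence. At stake is how far the icatibant and placebo columns of the safety table can be read against each other.

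**Working it through.** The article gives no figure on this point, so there is nothing to reproduce. The check is mainly a reading of the sections against each other.

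1. **Is attribution a condition of the definition?** Yes. In 2.10 the suspicion clause is part of what an adverse event is, not a grading made after recording. The signs, laboratory changes and worsening that follow are introduced as inclusions, so on the plain reading they fall under the same condition.

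2. **Does another section widen it?** No. Sections 2.7.3 and 2.8.5 use the term without redefining it. Physical findings and vital signs (2.7.3) are monitored outside the definition, but 2.8.5 specifies a by-phase summary for adverse events only.

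3. **Does the definition feed a comparison by treatment?** Yes. The term defined in 2.10 is the term counted by phase in 2.8.5.

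4. **Is the judgement blinded?** No blinding of it is described. The eye mask covers the participant, the investigator prepares and gives the drug (2.6), and evaluation falls to physicians (2.7.3). That the assessor knows the treatment is an inference from the single-blind design and the absence of a named blinded assessor; the article does not say so outright.

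5. **How narrow is the filter?** It is attribution to conducting the study, not to icatibant. Both phases include a subcutaneous injection, two thermal loads, blood sampling and the inpatient stay (2.6, 2.6.1, 2.6.2). Many events after saline could pass it.

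**Scale of one event.** With 10 patients treated in a phase (2.8.1), removing a patient's only event in that phase changes subject incidence by 1/10 = 10 percentage points. If the patient has another counted event in the phase, subject incidence does not move. The figure does not apply to the count of events.

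**Illustration, on assumptions that are not in the document.** Let each of n = 10 patients have the same true event risk p in both phases, and let an event be recorded with probability q(ica) or q(pla). Expected subjects are n × p × q; for example 10 × 0.30 × 0.9 = 2.7 and 10 × 0.30 × 0.6 = 1.8. The chances come from exact binomial counts, treating the phases as independent.

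| p | q(ica) / q(pla) | Expected subjects, icatibant v placebo | Chance icatibant higher | Chance placebo higher |
|---|---|---|---|---|
| 0.10 | 1 / 1 | 1.0 v 1.0 | 0.344 | 0.344 |
| 0.10 | 0.9 / 0.6 | 0.9 v 0.6 | 0.412 | 0.228 |
| 0.10 | 0.9 / 0.3 | 0.9 v 0.3 | 0.503 | 0.116 |
| 0.30 | 1 / 1 | 3.0 v 3.0 | 0.403 | 0.403 |
| 0.30 | 0.9 / 0.6 | 2.7 v 1.8 | 0.586 | 0.223 |
| 0.30 | 0.9 / 0.3 | 2.7 v 0.9 | 0.785 | 0.079 |
| 0.50 | 1 / 1 | 5.0 v 5.0 | 0.412 | 0.412 |
| 0.50 | 0.9 / 0.6 | 4.5 v 3.0 | 0.683 | 0.174 |
| 0.50 | 0.9 / 0.3 | 4.5 v 1.5 | 0.902 | 0.036 |

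If q is equal in the two phases, the expected difference is zero and only the level is lowered (at p = 0.30 and q = 0.6 in both, 1.8 v 1.8 instead of 3.0 v 3.0). If the two q values are swapped, the results mirror. The table shows that a differential filter could matter at this sample size, not that one operates.

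**The case against.** The strongest reply is that the filter is wide. A symptom after saline can be put down to the injection, the heat or the stay as readily as one after icatibant. Knowing the syringe content bears mainly on drug causality, which is not the stated test. This stands, and it is why the effect may be small. It does not remove the point: the Discussion says that transient injection site reactions are expected with icatibant, and 2.7.3 names icatibant, not saline, as a safety concern, so an unmasked assessor has some reason to judge by phase.

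A reader might go further and infer that icatibant will look worse than placebo, or that the by-phase table compares nothing real. The documents do not support either. They give no attribution rates, an unmasked assessor could also discount events on icatibant, and with equal attribution rates no bias in the difference arises.

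The consequence is also limited. The table is descriptive, safety is neither a primary nor a secondary endpoint, the study is a 10-patient proof of concept, and physical findings and vital signs lie outside the definition. All of this stands.

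Finally, the full protocol (v1.3) and the case report form are not shown, and relatedness may already be recorded there. That bears on the cost of the fix. It does not answer the point, which concerns a definition that the article states rather than a detail that it omits.

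**Conclusion.** The point holds as a defect in a stated definition. Section 2.10 makes suspected attribution a condition of being counted, 2.8.5 tabulates what is counted by treatment phase, and the only masking described is the participant's. Occurrences judged unrelated drop out of both phases, and the judgement may differ by phase.

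The size and direction of any resulting bias cannot be derived from the document, and the effect may be small because the filter covers the whole study, including the injection and thermal load. The one firm figure is 10 percentage points of subject incidence for a patient's only event in a phase, assuming that all 10 patients are treated in that phase. The conclusion also rests on the inference that whoever judges attribution may know the treatment. The descriptive safety table is affected; the primary endpoint and its error rate are not.

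**What to change.** **Section 2.10.** Define an adverse event as any untoward occurrence, whether or not thought related to the study. Record suspected attribution (drug, thermal load, other) as a separate item, preferably judged by someone unaware of the treatment. Keep the attribution-based category for statutory reporting.

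**Section 2.8.5.** Tabulate all events from the first study drug onward by phase, with suspected-related events as a subset. The first phase runs from the Day 1 injection to just before the Day 2 injection, and the second from the Day 2 injection to the Day 3 check. List events before the first study drug separately: the first Day 1 thermal load precedes any drug (2.6.1), so its events belong to neither phase. The third thermal load, on Day 2, falls within the first phase under this rule; onset times and the attribution item allow its events to be identified.

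**Cost.** A wording change in two sections, an attribution field if the case report form lacks one, and a few more minor events to record over a 3-day stay. Recording and detection stay unblinded, so the change removes the causal filter but not every influence of knowing the treatment. Section 4 gives a recruitment start in July 2021, so if patients have already been assessed under the present definition, the report should say which definition applied to them.

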## 3. Discussion

Sweating-induced dermal pain is triggered by daily events, such as bathing, exercise, and mental stress.^[1–3]^ It is transient but brings severe and heavy impacts on patients lives. The pathomechanism of sweating-induced dermal pain remains unclear, and no standard treatment has been established. Treatments may include antihistamines, steroid pulse therapy, psychotropic drugs, and the Ca^2+^ channel α2δ ligand, but their effectiveness is limited and varies among patients.^[1]^

Bradykinin is an endogenous substance that causes pain.^[15]^ Since predominant kinin-producing activity is detected in the skin during thermal sweating, bradykinin may play a role in pain during sweating stimulation.^[7–10]^ Icatibant, a bradykinin B2 receptor antagonist, has been approved for the treatment of acute attacks of hereditary angioedema,^[14,16]^ but been off-label for dermal pain associated with sweating stimuli. Subcutaneous administration of 30 mg icatibant results in a rapid increase in blood icatibant levels (Tmax 0.63 hour) and effectively inhibits bradykinin activity.^[14]^ If a subcutaneous injection of icatibant effectively reduces sweating-induced dermal pain, it would provide clear evidence for the involvement of the bradykinin-bradykinin B2 receptor pathway in this condition.

This study is a crossover, single-blind, placebo-controlled, randomized comparative study. Due to the rarity of patients with sweating-induced dermal pain, the number of patients capable to be enrolled in the study is limited. Moreover, the subjective nature of pain perception makes it difficult to compare pain levels across patients. To minimize these limitations, a crossover design is employed. Furthermore, to account for the potential placebo effect on dermal pain due to expectations of drug efficacy, the present study is designed as a single-blinded, placebo-controlled, randomized study.

The icatibant dose setting is based on its efficacy and safety. A pharmacodynamic analysis estimated the tolerated dosage needed to reduce bradykinin-induced reactions to be 0.4 mg/kg,^[14]^ that is, 30 mg for an adult. Moreover, the approved dose of icatibant for hereditary angioedema is 30 mg/dose and has no frequent harmful events, except for transient local injection site reactions.^[14,16]^ In this study, the same dosage of 30 mg used for hereditary angioedema is set for dermal pain. Since icatibant is typically administered as a single dose for hereditary angioedema attacks,^[14]^ the treatment in this study also includes a single administration of icatibant or placebo.

The primary endpoint is to assess the effectiveness of icatibant in treating sweating-induced dermal pain. Pain will be evaluated using a VAS score by inducing dermal pain with a thermal load before and after icatibant administration. This approach has been chosen due to the importance of evaluating pain in patients with the dermal pain and the subjective nature of pain perception. To induce dermal pain, both lower legs will be placed in warm water (~43°C) for 30 minutes.^[13]^ This condition of loading is enough to induce sweating in healthy subjects, commonly experienced in daily life, and thus, non-excessive in terms of intensity and duration. The VAS score, a widely used pain rating scale, will be employed to measure the intensity of the pain.

Blood histamine and ACE levels will be measured as biomarkers. Similar to bradykinin, histamine causes skin pain and may be associated with dermal pain.^[1]^ ACE is an enzyme involved in the kallikrein/kinin system that degrades and inactivates bradykinin.^[15]^ By analyzing the dynamics of these molecules before and after thermal sweating, we will evaluate the relationship between dermal pain occurrence, histamine in circulation, and the kallikrein-kinin system. Additionally, to explore the pathomechanism of dermal pain, we will examine histological changes of the eccrine sweat glands at the site of dermal pain in patients who provide consent for a skin biopsy. Histological analyses focus on pore obstruction, reduction in the number and atrophy of sweat glands, and surrounding inflammatory infiltration.^[1,17–19]^

A limitation of this study is that a small number of patients are planned to be enrolled. Since this preliminary study is conducted for proof of concept, only ten patients will participate to explore the effect of blocking kinin-bradykinin pathway to sweating-induced dermal pain. Moreover, the efficacy of icatibant in this study does not necessarily imply that the use of icatibant is a practical treatment for the pain due to its short effective duration of action. According to pharmacodynamic analysis, icatibant exerts its effectiveness for only 5.5 to 6 hours.^[14]^ This indicates that multiple administrations in a day are necessary for its clinical application. However, this is not realistic because icatibant is administered subcutaneously rather than orally and is expensive, thereby posing a high-cost burden for patients. Alternatively, this study may pave the way for novel treatments of dermal pain using kallikrein inhibitors. Kallikrein produces bradykinin by acting on high-molecular-weight kininogens; therefore, kallikrein inhibitors suppress the subsequent bradykinin-mediated responses.^[15]^ Kallikrein inhibitors berotralstat^[20]^ and lanadelumab^[21]^ are an oral formulation and a subcutaneous formulation with a considerably longer duration of effect, respectively.

Overall, this study contributes to a better understanding of the underlying mechanisms of sweating-induced dermal pain and has the potential to improve the quality of life for patients experiencing this debilitating condition by suggesting potential treatment options.

## 4. Trial status

The study was approved on December 22, 2020. Participant recruitment will begin on July 8, 2021. The expected date of completion is the end of December 2024. Central ethical approval was obtained from the Hiroshima University Certified Review Board (reference approval number: CRB6180006). The protocol and progress have been registered in Japan Registry of Clinical Trials (jRCT), jRCTs061210021 since July 8, 2022. Protocol version is v1.3 as on February, 2022.
